#### Prevalence Study

The specific objectives of this study include (1) evaluating the overall prevalence rate of workplace cyberbullying and its related psychological impacts (depression, anxiety, and stress) on TCM practitioner; (2) understanding the measures associated with various forms of workplace cyberbullying on age, gender, and frequency; and (3) understanding the measure associated with workplace cyberbullying on perpetrators responsible for workplace cyberbullying. The current research will be a survey-based online cross-sectional prevalence study. TCM practitioners are considered a hard-to-reach population; thus, we will conduct a nonprobability snowball sample of 1023 adults (3% precision, 95% confidence level) according to the number of TCM practitioners, which was approximately 15,000 in 2011 [16]. The Hamilton Depression Scale (HAM-D) [17], the Hamilton Anxiety Scale (HAM-A) [18], and the clinical anger scale [19] will be used to assess the psychological impact on TCM practitioners. The Cyberbullying Questionnaire (CBQ) and a short version of a cyberbullying behavior questionnaire (CBQ-S), adapted from Jönsson et al [20], will be used to identify the prevalence among TCM practitioners; these selected questionnaires were already validated in Sweden and the US adult population [20]. The prevalence will also investigate the association with moderating variables (age and gender). Perpetrators of cyberbullying will also be assessed in the specific identification of the prevalence of workplace cyberbullying using the CBQ and CBQ-S questionnaires. The sampling method to understand perpetrator effects in the prevalence will similarly be addressed. The survey will also include a socioeconomic assessment, including education, income, home characteristics, and commodities. The survey will be conducted online due to the current pandemic situation caused by COVID-19, following the CHERRIES guidelines given by Gunther Eysenbach [21].

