#### Exploratory Study

The purpose of the exploratory study is to understand the moderating and mediating factors of workplace cyberbullying by using the ERM on TCM practitioners [15]. The specific questions of this study include the following: (1) What are the relationships between emotions, workplace stressors, cyberbullying perpetration, cyberbullying victimization, and control appraisal, reappraisal, and suppression? (2) What effects do demographic factors have on emotions, workplace stressors, cyberbullying perpetration, cyberbullying victimization, and control appraisal, reappraisal, and suppression? The survey will be conducted using a convenience method, with a sample size of 384 (5% precision, 95% confidence level). A structural equation model will be developed, and each construct will be discussed. A snowball sampling method will be used to approach the target population. There will be a lucky draw at the end of the exploratory study on the participants; the 10 winners of the draw will receive an electronic power bank.

This procedure was selected due to a hard-to-reach study population and a study undertaken during the COVID-19 pandemic.

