#### Quasi-experiment with Nonequivalent Pretest–Post-test Control Group Design

The study design for this stage is quasi-experimental, in which the groups are nonrandomized into intervention and control groups and selected purposively. This study will be conducted in public hospitals and private hospitals located in Malaysia. All hospitals are eligible to participate. The selection of hospitals will be randomized for the implementation of the interventions. The randomization of hospitals will be performed by online statistical computing web programming to generate the randomization schedule [22]. The current methodology will help reduce selection bias in the study.

This intervention study will be conducted on TCM practitioners specifically. A baseline assessment will be done, in the intervention and control hospital, to measure the burden of bullying and its correlates using the CBQ and CBQ-S. This stage will begin after the investigation of prevalence and exploratory research. First, baseline information will be collected within 3 months, and then the intervention will be monitored twice after a regular period of 6 months in order to monitor the consistency of the intervention program.

The intervention program will be designed and finalized after (1) a systematic review of systematic reviews of previously published literature on bullying and the effectiveness of antibullying intervention programs; (2) the conducting of focus group discussions with TCM practitioners, patients, and other health care providers (to explore the perceptions, beliefs, and suggestions regarding bullying prevention programs); and (3) the conducting of a consultation workshop with all the stakeholders. The bullying intervention program (BIP) will pretest among 50 participants, which will include health care providers, TCM practitioners, and patients. The multicomponent hospital-based intervention strategy will be administered at 3 levels: (1) patients, (2) TCM practitioners, and (3) other health care providers. All the data of participants in this study will be password-protected and safe using Microsoft OneDrive. The recruitment of participants will follow the same procedure described for the exploratory study and prevalence study.

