#### Data Collection and Analysis

The recruitment of participants will follow the same procedure as was described for the exploratory study and prevalence study. The participant will be invited to join through a webinar to complete the questionnaire. Only the participants who completed Phase 2 will be asked to continue. The prototype will be given to them, and a brief training will be provided through a 30-minute webinar. Stage 3 participants will be limited to the Stage 2 completers in order to gauge the effectiveness of the Step 2 intervention program and whether the prototype is capable of reporting cyberbullying effectively. Thematic analysis will be done on the data yielded from the control and intervention groups. All the data of participants in this study will be password-protected and safe using Microsoft OneDrive.

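### Phase 2 carries snowball recruitment from the surveys into a comparison of intervention and control hospitals, so peer referral can decide who enters each arm

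*Protocol article*

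**What the plan says.** All references are to the protocol article.

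- **Phase 2 recruitment** (Quasi-experiment with Nonequivalent Pretest–Post-test Control Group Design): "The recruitment of participants will follow the same procedure described for the exploratory study and prevalence study".
- **What that refers back to.** The Prevalence Study section says "we will conduct a nonprobability snowball sample of 1023 adults (3% precision, 95% confidence level". The Exploratory Study section says "The survey will be conducted using a convenience method, with a sample size of 384 (5% precision, 95% confidence level", and then "A snowball sampling method will be used to approach the target population". The reasons given in Phase 1 are a population that is hard to reach and the COVID-19 pandemic.
- **How Phase 2 forms its groups.** The same Phase 2 section says that "the groups are nonrandomized into intervention and control groups and selected purposively", and two sentences later that "The selection of hospitals will be randomized for the implementation of the interventions". It then claims that the methodology will help to reduce selection bias.
- **Baseline.** "A baseline assessment will be done, in the intervention and control hospital, to measure the burden of bullying and its correlates".
- **Phase 3** (Data Collection and Analysis): "The recruitment of participants will follow the same procedure as was described for the exploratory study and prevalence study". The same paragraph restricts Phase 3 to people who completed Phase 2.

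**The concern.** In a cross-sectional survey, snowball sampling costs representativeness. In a comparison of two groups it also costs comparability, because the referral process can run differently in each group.

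Two things are at stake. The first is **selection**. If people in an intervention hospital know that the programme is coming, those who bring in colleagues, and the colleagues who accept, may be more motivated or more exposed to bullying than their counterparts in a control hospital. The outcome is itself a matter of relations between colleagues, so recruitment along friendship ties may select on something close to the outcome (CBQ, CBQ-S). The second is **contamination**. Referral chains follow social ties, these can cross hospitals, and the plan does not confine them.

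Selection at enrolment cannot be undone once recruitment has closed. Because Phase 3 takes only Phase 2 completers, any Phase 2 selection is carried into it.

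**Working it through.** Phase 2 states no figure on this point, so there is nothing to reproduce. The check is mainly a reading of the sections together, followed by one illustration.

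**Step 1. Is the recruitment method stated or merely inferred?** It is stated. The Phase 2 sentence points to the exploratory and prevalence studies. The prevalence study is a nonprobability snowball sample. The exploratory study is described as both convenience and snowball. No other recruitment route for TCM practitioners is given in Phase 2.

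**Step 2. What is the unit of comparison?** The hospital. The randomization schedule applies to hospitals, baseline is taken in an intervention and a control hospital, and the programme is described as hospital-based.

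**Step 3. Does randomizing hospitals protect against who enrols within them?** No. Suppose a trait shifts the outcome score by *d*, and is present in a share *p*₁ of those enrolled in intervention hospitals and *p*₀ of those enrolled in control hospitals. The bias in the group difference is

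*d* × (*p*₁ − *p*₀).

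Randomization makes *p*₁ and *p*₀ equal on average only if enrolment does not depend on the hospital's status. If referral responds to that status, the term does not shrink as hospitals or participants are added. The pretest removes only the part of it that shows in the baseline score. The documents give no value for *d*, *p*₁ or *p*₀, so no number follows.

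**Step 4. Is enrolment before or after hospital status is known?** The text does not give the order. Hospitals already carry the labels intervention and control when baseline is described, which is consistent with status being set by then but does not prove it. No sentence places enrolment before disclosure.

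**Step 5. Is referral confined to one hospital?** No sentence does so, and the Phase 1 procedure that Phase 2 inherits has no hospital boundary.

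**Step 6. Illustration of contamination, on assumed values only.** Let a share *c* of controls receive the full effect Δ. The control mean then moves by *c*Δ, so the observed difference is (1 − *c*)Δ. Required sample size varies with 1/(difference)², so it is multiplied by 1/(1 − *c*)².

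| Assumed *c* | Observed share of effect | Sample multiplier |
|---|---|---|
| 5% | 0.95 | 1/0.9025 = 1.11 |
| 10% | 0.90 | 1/0.81 = 1.23 |
| 20% | 0.80 | 1/0.64 = 1.56 |
| 30% | 0.70 | 1/0.49 = 2.04 |

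The documents give no value of *c*. A partly exposed control would dilute the effect less than the table shows.

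**Step 7. Consistency of neighbouring statements.** Groups that are nonrandomized and purposively selected do not sit with hospitals randomized for the intervention. In Phase 3, a procedure for finding new participants does not sit with a cohort closed to Phase 2 completers.

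**The case against.** The strongest reply has four parts.

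*The design declares itself nonequivalent.* It expects baseline differences and has a pretest to handle them, and the claim about selection bias can be read as referring only to the randomization of hospitals. This is fair as a description. It does not justify adding an avoidable source of imbalance, and a pretest does not correct selection on factors that the baseline score misses.

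*The order of allocation and enrolment is not in the text.* This stands. A reader might infer that participants are enrolled after allocation, but the wording about the intervention and control hospital may only name where baseline is measured. The flow diagrams that might show the order are not available here. The point is therefore a risk that the text leaves open, not a stated flaw.

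*Contamination is weakly supported.* This largely stands. Being referred by someone elsewhere does not deliver a hospital-based programme, and social ties between hospitals exist under any recruitment method. A reader might take the 10% to 30% range as an estimate of loss. It is not one, and the article gives no Phase 2 sample size to which the multiplier could be applied.

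*Some tempting premises are absent.* The article does not call the surveys anonymous, does not say that hospitals have agreed to take part, and does not say that hospitals can list their TCM practitioners. The point needs none of the first two. The third matters only for the ease of the remedy.

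It is also true that simply deleting the recruitment sentences would leave patients, other providers, the 50-person pretest and the Phase 3 stakeholder experts without recruitment wording.

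**Conclusion.** The point holds as a design weakness that should be corrected. The article itself fixes snowball and convenience recruitment for Phase 2, so this is not detail left to a fuller document. Used in a comparison of hospitals, the method lets peer referral shape the membership of each arm, and randomizing hospitals cannot repair that. It works against the section's own aim of reducing selection bias.

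The size of the selection bias is unknown and cannot be bounded from the document. The conclusion rests on the recruitment sentence meaning what it says, and on referral being able to respond to hospital status. The text neither states nor excludes the latter. Contamination is a secondary possibility of unknown size. The documents do not support the stronger reading that enrolment is known to follow allocation or that dilution will occur.

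The Phase 3 sentence is a wording inconsistency. The rule limiting entry to completers is clear, so it adds no weight to the Phase 2 point but should be tidied at the same time.

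**What to change.** 1. In the Phase 2 section, for TCM practitioners, replace the reference to Phase 1 recruitment with wording such as: *All eligible TCM practitioners at each participating hospital will be invited. Enrolment and baseline CBQ and CBQ-S will be completed before that hospital's allocation is disclosed to staff or recruiters. Participants will not be recruited by referral from another hospital.*
2. Keep separate recruitment wording for patients, other health care providers and the 50-person pretest.
3. Reconcile the two statements on allocation in the same section, so that it is clear whether hospitals are randomized or groups are chosen purposively. Enrolment before disclosure is useful in either case.
4. In the Phase 3 data collection section, limit the recruitment sentence so that it agrees with the rule that only Phase 2 completers continue, and cover separately any stakeholder experts who test the prototype.

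The cost is protocol wording and some administration at each hospital to reach all eligible practitioners. The article does not say whether hospitals hold such lists. Where one does not, an open notice to all eligible practitioners there would serve the same purpose. The real downside is confidentiality: the study concerns workplace bullying and Phase 1 also assesses perpetrators, so replies should go directly to the study team and the employer should not learn who takes part.

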### Phase 3: Electronic Anticyberbullying Monitoring System

#### Interface Design

An expert from each stakeholder group (TCM practitioners, other health care professionals, patients, and IT experts) will be involved in the interface design, information system design, and prototype testing. The system’s overall performance and satisfaction will be acquired through questionnaires (questionnaires are available upon request). The CBQ and CBQ-S will be used to determine the effectiveness of an intervention program using a prototype (post-test). The compilation of this research will be used to design the Personalized Mobile Mental Health Intervention (PMMH-I). The duration for stage 3 will be 6 months.

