**Objective:**

Our main objective is to study the pre-effects and posteffects of the Personalized Mobile Mental Health Intervention (PMMH-I) for workplace cyberbullying in public and private hospitals in Malaysia.

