**Results:**

The results of this study will determine the pre- and posteffectiveness of an integrated PMMH-I for health care professionals. The prototype system platform will be developed and implemented in a public and private hospital. Results from Phase 1 will be published in 2021, followed by the implementation of Phase 2 in subsequent years.

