### Research Questions

We aim to explore the following 4 research questions in this study: (1) What is the current workplace cyberbullying status among Traditional Chinese Medicine practitioners (TCM) in Malaysia? (2) What is the pre- and postefficacy of the Personalized Mobile Mental Health Intervention (PMMH-I) on the prevalence of measurable factors (ie, depression, anxiety, and stress) in workforce cyberbullying on TCM practitioners? (3) What are the moderating and mediating factors of workplace cyberbullying on TCM practitioners? (4) What is the technological feasibility of implementing the integrated PMMH-I as a component of routine hospital-based systems?

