### Phase 2: Program Development

#### Objectives

The aim of Stage 2 is to develop the anticyberbullying intervention program. Past approaches have been ineffective because of a lack of consistency within the community. To achieve this objective, a quasi-experiment with a nonequivalent pretest–post-test control group design will be conducted for a duration of 1-1.5 years (Figure 5).

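### The article promises an effectiveness result for PMMH-I, but as described its only controlled phase tests a bullying program and its prototype phase states no comparison group

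*Protocol article*

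**What the plan says.** Three places in the protocol article set PMMH-I as the thing to be evaluated.

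- Abstract, Objective: "Our main objective is to study the pre-effects and posteffects of the Personalized Mobile Mental Health Intervention (PMMH-I) for workplace cyberbullying".
- Abstract, Results: "The results of this study will determine the pre- and posteffectiveness of an integrated PMMH-I for health care professionals".
- Research Questions, item 2: "What is the pre- and postefficacy of the Personalized Mobile Mental Health Intervention (PMMH-I) on the prevalence of measurable factors", the factors being depression, anxiety and stress.

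The control group is in Phase 2. The Objectives there state "The aim of Stage 2 is to develop the anticyberbullying intervention program", and that for this purpose "a quasi-experiment with a nonequivalent pretest–post-test control group design will be conducted for a duration of 1-1.5 years". The section on the quasi-experiment gives the intervention a name only once: "The bullying intervention program (BIP) will pretest among 50 participants". It describes a hospital-based strategy with several components, delivered to patients, TCM practitioners and other providers.

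PMMH-I appears next under Phase 3, Interface Design: "The compilation of this research will be used to design the Personalized Mobile Mental Health Intervention (PMMH-I"). The same section uses the CBQ and CBQ-S as a post-test with a prototype. Under Data Collection and Analysis, only Phase 2 completers are invited to continue, and "The prototype will be given to them, and a brief training will be provided through a 30-minute webinar". Restricting entry to completers is meant both to gauge the Phase 2 program and to see whether the prototype can report cyberbullying.

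**The concern.** The intervention named in the objective and the intervention compared with a control group do not appear to be the same. If PMMH-I is designed from the results of the earlier work, it does not yet exist while the control group is being followed. When a prototype does exist, the article describes no one who is followed without it.

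At stake is the headline conclusion. Followed as written, the plan would lead to a statement on the effectiveness of PMMH-I resting either on a comparison of another program or on an uncontrolled post-test. A change in reported cyberbullying in Phase 3 could reflect the passing of time, lasting effects of the Phase 2 program, or the loss of non-completers. A reporting tool may also alter what people report.

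**Working it through.** The article gives no figure to reproduce on this point. The check traces, phase by phase, what is delivered, to whom, and against what.

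| | Phase 2 | Phase 3 |
|---|---|---|
| Intervention named | Anticyberbullying program, also called BIP | Prototype of an electronic monitoring system, apparently that of PMMH-I |
| Mobile component stated | No | Not stated for the prototype itself; PMMH-I is to be designed from the compiled work |
| Recipients | Intervention hospitals, at 3 levels | Phase 2 completers who continue |
| Comparator | Control hospitals | None stated |
| Analysis by group named in the Phase 3 text | Not applicable | Thematic (qualitative) only |

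The Study Plan and the main Results section both place prototype development in the last phase, which agrees with Interface Design. The count of controlled comparisons is therefore 1 for the bullying program and 0 for PMMH-I.

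Next, what could a Phase 3 post-test identify? Write P for the prototype effect, T for the time trend since the reference measurement, C for carry-over of the Phase 2 program among those who had it, and S for the shift that arises because only completers are measured. Assume for simplicity that T, S and P are the same in both Phase 2 groups. This favours the plan, since the groups are nonequivalent.

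- *Change within the former intervention group:* P + T + C + S. P is not separable.
- *Change within the former control group, if it receives the prototype:* P + T + S. P is not separable.
- *Between groups, if both receive the prototype:* (P + T + C + S) − (P + T + S) = C. P cancels, and what remains concerns the Phase 2 program.
- *Between groups, if former controls continue without the prototype:* (P + T + C + S) − (T + S) = P + C. The prototype and the Phase 2 program are estimated together.

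None of these readings of the Phase 3 text gives P alone from the post-test. The last line also shows that wait-listing the controls would not be enough: it would compare the Phase 2 program plus the prototype with neither.

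**The case against.** The strongest reply is that PMMH-I is the name of the whole program, so that Phase 2 does test it against control. There is support for this. Main Intention and Objective describes PMMH-I as the program to be developed and implemented. The literature review under Phase 3 presents a personalized mobile approach as the intervention. The caption of Figure 3, the diagram of the experimental design, spells out the abbreviation PMMH-I, so the figure probably contains it. Figures 3 and 5 are not available here, and the BIP label occurs only once. This stands as a possible intention. It does not settle the matter, because the Phase 2 text describes a program with no mobile element and Interface Design treats PMMH-I as still to be designed. On that reading the sections contradict one another.

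A reader might go further than the text in three ways:

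- *That PMMH-I is designed only after Phase 3 ends.* The sentence sits inside the Phase 3 section, so in or after Phase 3 is as far as it goes.
- *That both groups receive the prototype, so the between-group contrast is zero by design.* The article says completers receive it and still mentions data from control and intervention groups. Handing it to everyone is a fair inference, not a stated rule, and the groups would still differ in Phase 2 exposure.
- *That regression to the mean is built in.* Entry to Phase 3 is by completion, not by a high CBQ score.

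It is also fair to say that Phase 2 has its own monitoring rounds, so the Phase 3 post-test need not be the only measure of the Phase 2 program, and that the abstract's objective speaks of pre- and post-effects rather than a between-group effect. But the abstract's Results and the second research question speak of effectiveness and efficacy, which an uncontrolled before-after change does not establish.

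**Conclusion.** The point holds. As described, the article promises an effectiveness result for PMMH-I and contains no controlled comparison of it. The Phase 3 post-test mixes any prototype effect with time trend, carry-over and completer selection. The size of the resulting bias cannot be stated, since no effect size, trend or dropout figure is given for Phase 2 or 3.

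The conclusion rests on two assumptions: that the Phase 2 program is not PMMH-I, and that the Phase 3 prototype is PMMH-I's. If the first is wrong, the controlled comparison does concern PMMH-I, and the defect becomes a contradiction between sections that still has to be resolved. If the second is wrong and the prototype is only a monitoring tool, PMMH-I is not tested in any phase and the gap is wider. On every reading the text must change before results are reported under the present objective.

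**What to change.** 1. State plainly whether the Phase 2 program is PMMH-I, and make the Phase 2 sections, Interface Design, Main Intention and Objective, the literature review and the Figure 3 caption agree.
2. If it is not, restate the objective, the second research question and the expected results. Phase 2 estimates the effect of the bullying intervention program against control, using a CBQ/CBQ-S post-test taken in both groups before any prototype is handed out. Phase 3 is an uncontrolled feasibility and usability test of the prototype, with no effectiveness claim.
3. State which Phase 2 completers receive the prototype.

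The cost is a change of wording, a fixed time for the Phase 2 post-test (already implied by the pretest–post-test design), and a narrower headline claim. The fourth research question, on technological feasibility, fits the narrower role of Phase 3.
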